## **9. Safety evaluation**

### **9.1 Adverse events**

An adverse event (AE) is any untoward medical occurrence in a subject administered an investigational product and which may manifest itself by symptoms,

signs, disease, or laboratory abnormalities and which do not necessarily have a causal relationship with the investigational product. AEs in this trial should be collected from the time the subject signs the informed consent form to 30 days after initiation of treatment or initiation of treatment for a new target indication.

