### TQB2858 Injection Phase Ib Trial Subject Visit Schedule

| Item                             | Screening [1] | Treatment period |      |       |          |         |          |              |          |              |          | Follow-up period        |                           |                        |
|----------------------------------|---------------|------------------|------|-------|----------|---------|----------|--------------|----------|--------------|----------|-------------------------|---------------------------|------------------------|
|                                  |               | Cycle 1          |      |       |          | Cycle 2 |          | Cycle 2n + 1 |          | Cycle 2n + 2 |          | Out Visit [2]           | Safety follow-up [3]      | Survival Follow-up [4] |
|                                  |               | C1D1             | C1D7 | C1D14 | C1D21    | C2D1    | C2D21    | D1           | D21      | D1           | D21      | Early Withdrawal or D28 | 12 weeks after medication | Every 8 weeks          |
| Check Window [21]                | -             | -                | -    | -     | ± 3 days | -       | ± 3 days | -            | ± 3 days | -            | ± 3 days | + 7 days                |                           |                        |
| Informed Consent                 | X             |                  |      |       |          |         |          |              |          |              |          |                         |                           |                        |
| Height, weight [5]               | X             | X                | X    | X     | X        | X       | X        | X            | X        | X            | X        | X                       |                           |                        |
| Demographics/Medical History [6] | X             |                  |      |       |          |         |          |              |          |              |          |                         |                           |                        |
| ECOG score                       | X             |                  |      |       |          |         | X        |              |          |              | X        | X                       |                           |                        |

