| Concomitant medication | X             | X                | X    | X     | X        | X       | X        | X            | X        | X            | X        | X                       |                           |                        |
| Adverse events         | X             | X                | X    | X     | X        | X       | X        | X            | X        | X            | X        | X                       |                           |                        |

| Item                             | Screening [1] | Treatment period |      |       |          |         |          |              |          |              |          | Follow-up period        |                           |                        |
|----------------------------------|---------------|------------------|------|-------|----------|---------|----------|--------------|----------|--------------|----------|-------------------------|---------------------------|------------------------|
|                                  |               | Cycle 1          |      |       |          | Cycle 2 |          | Cycle 2n + 1 |          | Cycle 2n + 2 |          | Out Visit [2]           | Safety follow-up [3]      | Survival Follow-up [4] |
|                                  |               | C1D1             | C1D7 | C1D14 | C1D21    | C2D1    | C2D21    | D1           | D21      | D1           | D21      | Early Withdrawal or D28 | 12 weeks after medication | Every 8 weeks          |
| Check Window [21]                | -             | -                | -    | -     | ± 3 days | -       | ± 3 days | -            | ± 3 days | -            | ± 3 days | + 7 days                |                           |                        |
| Biomarker Sample collection [20] | X             |                  |      |       |          |         |          |              |          |              |          |                         |                           |                        |

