## Notes:

1. Within 28 days after signing the informed consent form, it belongs to the screening period;
2. For details about the out-group visit, see [Chapter 6 for details](#);
3. Safety visit: The safety follow-up period is the interval between the EOT visit and the scheduled follow-up visit, which should occur 30 days (± 7 days) after the EOT visit or 30 days (± 7 days) after study drug administration if the EOT visit was not performed.
4. Survival Visit: The first survival follow-up period (including telephone follow-up) will occur 8 weeks (± 7 days) after the last safety follow-up and occur every 8 weeks (± 7 days) until the subject has died, is lost to follow-up, the sponsor terminates the study, or other study closure criteria are met, whichever occurs first.
5. Height and weight: Height will be measured only during the screening period;
6. Demographics/medical history: Demographic data include date of birth, age, gender, ethnicity and occupation; medical history includes previous treatment regimen, concomitant diseases and treatment, allergy history and smoking history;

7. Vital signs: including body temperature, pulse, respiration and blood pressure;
  8. Physical examination: see [Chapter 6 for details](#);
  9. Infectivity test: hepatitis B virus, HCV and HIV; if HBsAg or HBeAg is positive, HBV DNA test should be performed; if HCV antibody is positive, HCV RNA test should be performed;
  10. Blood routine: See [Table 5 for details](#);
  11. Blood biochemistry: See [Table 5 for details](#);
  12. Thyroid function: See [Table 5 for details](#);
  13. Coagulation function: See [Table 5 for details](#);
  14. Urinalysis: see [Table 5 for details](#);
  15. Stool routine: see [Table 5 for details](#);
  16. Cardiac function: See [Table 5 for details](#);
  17. ECG: If chest pain, palpitation and other symptoms occur, echocardiography, myocardial enzyme spectrum and troponin should be additionally examined;
  18. Imaging examination: see [6.3 for details](#);
  19. Study drug: 3-week treatment cycle, administered on Day 1 of each cycle via intravenous drip, q3w; see details [5.4 Section content](#) ;
  20. Biomarkers: see [Chapter 7 for details](#) ;
- Check window period: the time window allowed for the visit on the specified visit day. If the specific item has the time window requirement, implement it according to the specific item requirement

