#### **4.3.3 Discontinuation from Study or Study Treatment of Steps**

If a subject was withdrawn from the study or discontinued study treatment, the following actions were taken:

1. The reason (s) must be documented in the medical file and eCRF;
2. An End of Treatment (EOT) visit should be performed. Tests done during the window before treatment withdrawal do not need to be done at the EOT visit. Inspections completed above, refer to the trial visit schedule;
3. The subject should be followed for safety for 30 days after the EOT visit or the subject starts a new anticancer therapy;
4. Subjects without disease progression should continue to undergo imaging evaluation at the scheduled frequency and time until the patient starts new anti-tumor treatment or disease progression. Every effort should be made to obtain imaging evidence of disease progression in such subjects;

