### 6.2.6 Follow-up Visit

After the end of treatment visit, enter the follow-up period. The safety follow-up period is the interval between the EOT visit and the scheduled follow-up visit, which should occur 30 days ( $\pm 7$  days) after the EOT visit or 30 days ( $\pm 7$  days) after study drug administration if the EOT visit was not performed. Adverse events and SAEs must be reported to at least 30 days after initiation of study drug, the date of the follow-up visit, or until the toxicities resolve, return to baseline, or are deemed irreversible, whichever is longer. Reasonable efforts should be made to have the subject return for the follow-up visit and report all AEs that occur during this period.

If a subject is scheduled to start a new antineoplastic therapy before the end of the safety follow-up period, the safety follow-up visit should be performed before the start of the new antineoplastic therapy. Once new antineoplastic therapy was initiated, subjects entered the survival follow-up period.

After completion of the safety follow-up period, enter into the survival follow-up

period. The first survival follow-up period (including telephone follow-up) occurred 8 weeks ( $\pm 7$  days) after the last safety follow-up and occurred on an 8-week ( $\pm 7$  days) basis until the subject died, lost to follow-up, the study was terminated by the sponsor, or other study closure criteria were met, whichever occurred first. The investigator may follow up the subject, his/her family or the responsible physician by phone to collect whether other anti-tumor treatment was given to the subject before this visit. If other treatments are used, the treatment regimen and cycle number and outcome must be recorded. The patients were followed up until death, and the relevant cause of death and specific time were recorded to obtain overall survival (OS).

For subjects who discontinue study treatment due to intolerance or other reasons, if no radiographic progression is observed, radiographic assessment should still be performed at the original frequency until disease progression or initiation of other anti-tumor therapy (except anti-tumor therapy with traditional Chinese medicine), and radiographic evidence of disease progression should be obtained as much as possible for such subjects.

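### The visit table and its own note 3 date the safety follow-up visit differently, and section 9.1 counts the end of AE collection from the start of treatment

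*Protocol*

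**What the plan says.** **Date of the safety visit.** In the Subject Visit Schedule, the safety follow-up column carries the timing "12 weeks after medication" and a pointer to note 3. Note 3 describes a visit "which should occur 30 days (± 7 days) after the EOT visit", with the fallback "30 days (± 7 days) after study drug administration if the EOT visit was not performed". Section 6.2.6 repeats both parts of note 3.

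**End of AE collection.** Section 9.1 states: "AEs in this trial should be collected from the time the subject signs the informed consent form to 30 days after initiation of treatment", or to the start of treatment for a new target indication. Three other places point elsewhere:

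- Section 4.3.3: "The subject should be followed for safety for 30 days after the EOT visit or the subject starts a new anticancer therapy". It gives no window and names no visit.
- Section 6.2.6 sets these limits for AE and SAE reporting: "at least 30 days after initiation of study drug, the date of the follow-up visit, or until the toxicities resolve". It adds two more, recovery to the baseline state and a judgement that the toxicity is irreversible, and the longest of them all governs. Sites should also have the subject return and "report all AEs that occur during this period", meaning the safety follow-up period.
- The visit table: the AE row is marked at every treatment visit and at the out visit. No row is marked in the follow-up columns.

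**Concomitant medication.** Section 5.5.4 uses *initiation* for a recording period that begins at withdrawal and closes 28 days after initiation of study drug or at the start of other antineoplastic therapy. The next row expresses the same boundary as an administration of 28 mg, which is not a time.

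**The concern.** A site working from the visit table and a site working from the notes or section 6.2.6 would schedule the same safety visit on different dates. The table and its note are both current instructions, and nothing says which prevails.

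The wording of 9.1 adds a second uncertainty. Section 9.3 tells investigators to collect AEs during the reporting period stipulated in the protocol, and 9.1 and 6.2.6 define that period differently. The incidence of AEs, SAEs and TEAEs is a secondary endpoint, and the TEAE definition in section 11.3.5 has no end date. The collection period therefore decides which late events are counted. An analysis plan cannot recover events that sites did not collect.

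**Working it through.** No sample size, power or error rate is involved. The check is calendar arithmetic and a comparison of sections.

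**1. Table header against note 3, no EOT visit**

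This is the only case in which both texts count from dosing. Assumption: medication in the header and study drug administration in note 3 are the same event, the last dose.

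- Header: 12 × 7 = day 84.
- Note 3: day 30, with window 30 − 7 = 23 to 30 + 7 = 37.
- Nominal gap: 84 − 30 = 54 days.
- Range: 84 − 37 = 47 to 84 − 23 = 61 days.

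**2. Table header against note 3, EOT visit held**

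Let X be the days from last dose to the EOT visit. Note 3 puts the safety visit at X + 30 (± 7), so the nominal gap is 84 − (X + 30) = 54 − X. The protocol does not fix X. Section 6.2.5 sets the EOT visit within 7 days after the end of treatment, but 5.4.2 lets a dose be delayed for up to 12 weeks before permanent discontinuation, so the end of treatment can fall well after the last dose. The two texts coincide within the window only if X happens to lie between 84 − 37 = 47 and 84 − 23 = 61 days. If instead the D28 (+ 7) of the out-visit column is counted from the last dose (an assumption), the latest safety visit is 28 + 7 + 37 = day 72, still short of 84.

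**3. Section 9.1 read literally**

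With C1D1 as day 1, 30 days later is day 31. Cycle 1 is 21 days, so this is 31 − 21 = cycle 2 day 10, before the C2D21 visit on day 42. The visit table collects AEs in every later cycle, so the literal reading contradicts the schedule as well as 4.3.3 and 6.2.6.

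**4. Is *initiation* a translation slip?**

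In 5.5.4 the literal word gives a period that is over before it begins for anyone who withdraws more than 28 days after the first dose. A meaning such as *end* or *last dose* makes the sentence work. The same reading repairs 9.1 and 6.2.6.

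**5. Would changing the single word settle it?**

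Not fully. Section 9.1 would count from the end of treatment and 4.3.3 from an EOT visit 0 to 7 days later, so the end points would differ by (0 + 30) − 30 = 0 to (7 + 30) − 30 = 7 days. In 5.5.4 the figure is 28 days against 30 elsewhere, a difference of 2 days in the text. Both are small, but they are a reason to name one anchor.

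**The case against.** The strongest reply is that the protocol largely corrects itself. *Initiation* is visibly a translation slip in a text with several others. AE marks at every treatment visit rule out stopping in cycle 2. Section 6.2.6 lets the longest limit govern and asks for all AEs up to the follow-up visit. Section 4.3.3 independently requires 30 days of safety follow-up after EOT. Safety is a secondary objective, summarised descriptively in a single arm.

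Most of this stands, and it rules out several stronger readings:

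- A reader might infer that AE data after day 30 of treatment will be lost. The visit table and 6.2.6 do not support that.
- A reader might infer that AEs go uncaptured throughout the 23 to 37 days after EOT. That requires the literal reading of 9.1, which is the improbable one. If *end* is meant, the difference from 4.3.3 is at most 7 days.
- A reader might apply the 54-day gap to every subject. It belongs to the fallback without an EOT visit.
- A reader might take the blank AE cell under safety follow-up as an instruction not to collect. Every follow-up cell is blank, so the column is incomplete and says nothing specific about AEs.

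The reply does not reach the header. No reading of *initiation* changes a 12-week heading into 30 days. Nor does it say whether 9.1 or 6.2.6 prevails.

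**Conclusion.** The point holds in a limited form. The main defect is the date of the safety visit: day 84 by the table header against day 30 (23 to 37) by note 3, 54 days apart (47 to 61) when no EOT visit was done. This assumes that both texts count from the same last dose. When an EOT visit is done there is no single figure.

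The second defect is the anchor in 9.1, repeated in 6.2.6 and 5.5.4. It is probably mistranslated and is contained by 6.2.6, so what remains is a risk that sites capture late AEs inconsistently. The documents give no basis for estimating how many events that would affect. The response endpoint is untouched. Because these are operative instructions for a safety endpoint and the correction is cheap, they should be fixed.

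**What to change.** - **Visit table header:** set it to 30 (± 7) days after EOT, or after the last dose where there was no EOT visit.
- **Sections 9.1 and 6.2.6:** replace *initiation* so that AEs are collected through the safety follow-up visit. If that visit is missed, collection ends 30 days after the EOT visit, or after the last dose if there was no EOT visit. Keep ± 7 days as a window for the visit only; it should not define the AE cutoff.
- **New anticancer therapy:** state that collection of new AEs stops when it starts, with the safety visit held beforehand as 6.2.6 already requires. Ongoing AEs are followed under 9.4.
- **Visit table cells:** mark AEs and concomitant medication in the safety follow-up column.
- **Section 5.5.4:** correct both the *initiation* wording and the 28 mg entry to the same end point.

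The cost is wording in three sections, one header and two table marks. The safety visit already exists, so no procedure is added.

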## 9.2 Evaluation of Adverse Events

The nature and severity of adverse events were evaluated according to the National Cancer Institute Common Terminology Criteria for Adverse Events (NCI-CTCAE v5.0). Items that cannot be assessed by this criterion can be assessed by the following criteria:

Table 6 Unlisted in NCI-CTCAE v5.0 Criteria for Judging the Severity of Adverse Events

| CTCAE Level | Degree Level               | Definition                                                                                                                                                                                                                         |
|-------------|----------------------------|------------------------------------------------------------------------------------------------------------------------------------------------------------------------------------------------------------------------------------|
| Level 1     | Mild                       | Discomfort that does not interfere with daily activities.                                                                                                                                                                          |
| Grade 2     | Moderate                   | Discomfort that decreases or interferes with usual activities; there is no indication for treatment or medical intervention, although it may improve the subject's general state of health or symptoms.                            |
| Grade 3     | Severe                     | Inability to work and perform usual activities; indications for treatment or medical intervention to improve overall health status or symptoms; delay in starting treatment does not put the patient's survival at immediate risk. |
| Grade 4     | Life-threatening/disabling | Permanent mental or physical condition that is immediately life-threatening or results in disruption of work or normal daily activity; requires medical or medical intervention to maintain survival.                              |
| Grade 5     | Death                      | Adverse events may result in death.                                                                                                                                                                                                |

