### Treatment Emergent Adverse Events (TEAE)

A TEAE was defined as an adverse event that appeared after or worsened after study drug administration.

a) The following adverse events were summarized by actual treatment:

- All adverse events (AEs);
- Treatment-emergent adverse events (TEAEs);
- TEAE judged to be DLT
- Grade 3 and above TEAEs;
- Serious adverse events (SAEs);
- TEAE leading to dose interruption and termination;
- TEAEs related to the study drug;
- Grade 3 and above TEAEs related to the study drug;
- SAEs related to the study drug;
- TEAEs related to the study drug leading to dose interruption and termination;

b) Describe the number and incidence of adverse events listed above by dose group, sorted by system organ class SOC and preferred term PT.

c) Number of cases and incidence of each toxicity grade of NCI CTCAE version 5.0 will be calculated according to actual treatment group, SOC and PT classification, respectively (for repeated occurrence of the same AE, the number of cases with the highest grade and the toxicity grade of the incidence will be analyzed).

d) Analysis of time to first TEAE

Time to first TEAE = date of first TEAE – date of first dose + 1. The analysis will be performed at overall level and at SOC and PT level. Only TEAEs judged as DLT will

be analyzed.

Provide detailed list of subjects with adverse events and detailed list of subjects with SAE.

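### Table 6, the fallback severity scale, defines Grade 5 (Death) by possible death and limits Grade 4 to permanent conditions, so the Grade 4/5 split is unreliable; a separate gap lies between Grades 2 and 3

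*Protocol*

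**What the plan says.** Section 9.2 grades adverse events by NCI-CTCAE v5.0 and offers Table 6 as a fallback: "Items that cannot be assessed by this criterion can be assessed by the following criteria". The rows that matter here are:

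- **Grade 2 (Moderate):** "Discomfort that decreases or interferes with usual activities". The row adds that treatment is not indicated, although it might help the subject.
- **Grade 3 (Severe):** the subject cannot work or carry on usual activities, and treatment is indicated. The row closes with the condition "delay in starting treatment does not put the patient's survival at immediate risk", which keeps events of immediate danger out of this grade.
- **Grade 4:** the label reads "Life-threatening/disabling". The definition then narrows this to the following: "Permanent mental or physical condition that is immediately life-threatening or results in disruption of work or normal daily activity". A further clause adds that intervention is needed to keep the subject alive.
- **Grade 5:** the label is Death, but the definition given beside it is "Adverse events may result in death".

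Section 11.3.5 plans a summary of "Grade 3 and above TEAEs", the same summary for drug-related events, and a table of cases and incidence at every toxicity grade. The Protocol Abstract (Data Analysis and Statistical Methods) also plans a separate summary of treatment-emergent events leading to death.

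**The concern.** A severity scale should give each event one row, and each row's definition should match its label. Table 6 fails in two places.

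At the top of the scale, Grade 5 is labelled by an outcome but defined by a possibility, while Grade 4 is narrowed by the word permanent. A life-threatening event that resolves has no natural place. Section 9.6.1 makes the contrast plain: there an event is serious if it threatens life, with no requirement that the condition be permanent.

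In the middle, Grades 2 and 3 each join a functional criterion to a treatment criterion, and the two pairings do not cover all combinations.

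At stake are descriptive safety outputs. Safety is the secondary objective and adverse-event incidence a secondary endpoint. Investigators assign the grade and record it in the CRF (Section 9.3), so a later analysis plan cannot by itself repair grades given under unclear definitions.

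**Working it through.** The plan gives no figure that depends on this wording, so there is none to reproduce. The check places typical events against the rows and then follows them into the outputs. Within a row, all clauses are taken to apply together.

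**Placement**

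1. *Reversible life-threatening event, survived.* Grade 3 is ruled out because survival is at immediate risk. Grade 4 is ruled out because the condition is not permanent. Grade 5 as defined fits, although the subject is alive.
2. *Permanent life-threatening condition needing intervention for survival, subject alive.* Grade 4 fits. Grade 5 as defined fits too, against its label.
3. *Fatal event.* Grade 5 by label and by definition.
4. *Event that is not life-threatening, interferes with usual activities and has an indication for treatment, in a subject who can still work.* Grade 2 is ruled out by the indication for treatment. Grade 3 is ruled out because the subject can work. Grade 4 is ruled out because no intervention is needed for survival. No row fits. (If activities are not affected at all, Grade 1 fits, since that row is silent on treatment.)

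**Effect on outputs**

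Let n3, n4 and n5 be the counts at Grades 3, 4 and 5, and suppose k events of types 1 and 2 are put in Grade 5 rather than Grade 4.

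- Grade 3 or higher: n3 + (n4 − k) + (n5 + k) = n3 + n4 + n5, so it is unchanged.
- Per-grade table: Grade 4 falls by k and Grade 5 rises by k.
- Fatal-event summary: unchanged, because these subjects survived. The Grade 5 count then exceeds the fatal count by k.

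For type 4, a choice of Grade 3 rather than Grade 2 adds a subject to the Grade 3-or-higher count, provided that subject has no other event at that level.

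**Size per subject**

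Using sample sizes from Section 11.2 (smallest cohort 10; largest size of Cohorts 1 and 2, and smallest total, 30; largest total 100):

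- 1/10 = 10 percentage points
- 1/30 = 3.3 percentage points
- 1/100 = 1 percentage point

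The n = 10 figure assumes that safety is tabulated by cohort, which Section 11.3.5 does not state. These are the effects of any one misclassified subject; they do not estimate how many there will be.

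**The case against.** The strongest reply is that the reach is small. Table 6 is permissive and applies only where CTCAE v5.0 does not. Fatal events have their own recording rule (Section 9.3) and their own summary, and Section 9.4 requires the outcome of every event, so a surviving Grade 5 subject would show up against the recorded outcome. A grader who sees a row labelled Death is unlikely to use it for someone alive. No hypothesis test is planned (Section 11.3.2), and neither the early-termination reasons (Section 4.8) nor the delay rule (Section 5.4.2) refers to a Table 6 grade. The wording may simply be a translation slip. All of this stands, and it limits the priority. It does not make the definitions correct.

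A reader might infer more than the text supports:

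- **That the Grade 4/5 confusion distorts the Grade 3-or-higher counts.** It cannot; both grades are above the cut.
- **That one event could be graded 2, 3 or 4, because Grade 4 mentions disruption of work or daily activity.** This overlooks that row's closing clause, "requires medical or medical intervention to maintain survival". With all clauses applied, Grade 2 has no indication for treatment, Grade 3 has one without immediate risk to survival, and Grade 4 needs intervention for survival. The rows do not overlap in that way.
- **That every survived life-threatening event is forced into Grade 5.** A permanent one fits Grade 4.
- **That any treated event in a working subject has no row.** Grade 2 allows that treatment may help without being indicated. The gap is confined to events where treatment is indicated.

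One could instead read Grade 4's closing clause as a sufficient criterion on its own. A reversible event needing life-saving intervention would then fit Grade 4, but it would still also fit Grade 5 as defined, so the split would remain unclear.

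**Conclusion.** The point holds as an inconsistency of wording with limited reach. For events outside CTCAE v5.0, the Grade 5 definition contradicts its label and the Grade 4 definition leaves out reversible life-threatening events. The Grade 4 and Grade 5 counts are therefore not well defined and can conflict with the fatal-event summary; Grade 3-or-higher totals are not affected by this. Those totals are exposed only through the gap between Grades 2 and 3.

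The number of affected events is unknown, since the protocol does not say how many events CTCAE v5.0 will fail to grade; it is probably small. The conclusion rests on a literal reading in which all clauses of a row apply together. Graders who follow the labels would avoid the Grade 4/5 problem, but the labels do not settle the Grade 2/3 gap as clearly.

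**What to change.** Correct Table 6 as follows:

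- **Grade 5:** the event resulted in death.
- **Grade 4:** life-threatening at the time of the event, whether or not the condition is permanent.
- **Grades 2 and 3:** state which row takes an event for which treatment is indicated but the subject can still work, so that every such event has one place.

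Carry the corrected table into the eCRF completion guideline. Before analysis, check events already graded with Table 6: compare Grade 4 and Grade 5 entries with the recorded outcome, and review Grade 2 and Grade 3 entries against the new boundary. The cost is one table correction and a short review of what should be few events.
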